**Fig. 1 Fig1:**
[figure not shown]
Consolidated standards of reporting trials (CONSORT) flowchart of the research procedure. fMRI, functional magnetic resonance imaging; GPM, Good Psychiatric Management; TAU, treatment as usual

The remaining assessments concern secondary outcomes and include the Outcome Questionnaire-45 [82], which is a self-report questionnaire comprising 45 items aiming at assessing psychotherapeutic results, including a global score and three sub-scale scores: symptomatic level, interpersonal relationships and social role. It has been translated and validated in French [83]. The Borderline Symptom List (BSL-23) [84] is a self-report questionnaire assessing the BPD symptomatology using 23 items; it represents a short version of the more extensive Borderline Symptom List [85] for which excellent psychometric properties were reported. Similar results were found for the short version used in this study [84]. The French version has shown comparable validity coefficients [86]. The Inventory of Interpersonal Problems (IIP) [87] (French translation by Stigler) is a self-report questionnaire assessing interpersonal patterns on several dimensions, such as affirmation, affiliation, submission, intimacy, responsibility and control. In total, this questionnaire comprises 64 items*.* Spielberger State-Trait Anger Inventory (STAXI-2) [88] is a self-report questionnaire on trait and state anger, using 44 items. This was translated to French and adapted by Borteyrou, Bouchon-Schweitzer and Spielberger [89]. The Difficulties in Emotion Regulation Scale [DERS] [90] is a self-report questionnaire assessing the quality of emotion regulation using 36 items. The French translation and validation of this instrument yielded a satisfactory factor structure on a student sample [91]. As a measure of the therapeutic alliance, the Working Alliance Inventory (WAI) [92] (French validation [93]) will be given after each session; the therapeutic alliance will be introduced as moderator where appropriate. At intake, reliable psychiatric diagnoses (using the Structured Clinical Interview for DSM-5 (SCID-5-CV) and Structured Clinical Interview for Personality Disorders (DSM-5) (SCID-5-PD) developed by the American Psychiatric Association), childhood trauma (Childhood Trauma Questionnaire [94]; French version [95]), rejection sensitivity (Rejection Sensitivity Questionnaire-Adult [96]) and the level of intelligence (National Adult Reading Test (NART), French version [97]) will be assessed.

Manipulation checks will be introduced by using self-report questionnaires of arousal (SAM [98]), self-esteem (SSES [99]) and vividness (Vividness of Visual Imagery Questionnaire (VVIQ) [100, 101]).

### Participant timeline {13}

Assessments take place at intake, 2 months and discharge, plus at follow up after 12 months. At follow up, the participants will be contacted by the research team; see {18b}. Importantly, any participant who dropped out of treatment will still be contacted for research assessments and follow up.

### Sample size {14}

Based on power analysis (presumed power 0.819, for two concomitant mechanisms, *d* = 0.60; two-tailed alpha = .05; 30% dropout), we plan to recruit 80 patients with BPD for this study at the Department of Psychiatry, University of Lausanne, Switzerland. In total, 10 therapists (psychiatrists or psychologists) will participate in the study for the GPM treatment; they have had at least 6 h of specific training in psychiatric treatment for BPD [102], in addition to training in psychotherapy according to Federal regulations.

### Recruitment {15}

Participants will be recruited at the Department of Psychiatry, University of Lausanne, Switzerland, in a specialized clinic for the treatment of BPD. The current patient flow will guarantee recruitment in the protocol. Patients are paid CHF70 for full participation in an assessment point.

## Assignment of interventions: allocation

### Sequence generation {16a}

A system involving computer-generated random numbers (block randomization in blocks of 10) was used at the outset and the allocation numbers were put into sealed envelopes. The latter are opened by the researcher upon patient inclusion. Patients are not stratified a priori.

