### Concealment mechanism {16b}

The sequence is concealed within sealed envelopes, which were prepared by a trial-independent researcher.

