### Implementation {16c}

The allocation sequence is generated by the computer, the concealment by an independent researcher. Then the study researchers enroll the participants and assign participants to interventions, after the opening of the sealed envelope.

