## Assignment of interventions: blinding

### Who will be blinded {17a}

The assessors (of outcome and mechanisms) and data analysts will be blind to the experimental condition, but the patients and the therapist will not. In order to control for bias, assessors will be polled at the end of the study with regard to each patient’s condition.

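### A single stated block size of 10, with enrolling researchers opening the envelopes at one clinic, could let up to about one allocation in six be deduced before enrolment

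*Protocol article*

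**What the plan says.** All of this is in the protocol article.

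- **Sequence generation {16a}:** "block randomization in blocks of 10) was used at the outset and the allocation numbers were put into sealed envelopes". Only one block size is given. The section adds "Patients are not stratified a priori", so there is one running sequence. On the envelopes it says "The latter are opened by the researcher upon patient inclusion".
- **Concealment mechanism {16b}:** "The sequence is concealed within sealed envelopes, which were prepared by a trial-independent researcher".
- **Implementation {16c}:** "Then the study researchers enroll the participants and assign participants to interventions, after the opening of the sealed envelope". Enrolment and assignment are therefore in the same hands.
- **Who will be blinded {17a}:** assessors of outcome and mechanisms, and data analysts, are blind, "but the patients and the therapist will not". Assessors are also asked at the end of the study about each patient's condition.
- **Recruitment {15} and Sample size {14}:** one specialised clinic in one department, 80 patients planned.
- **Who will take informed consent? {26a}:** a researcher explains the study and the randomisation to the patient.
- **Trial status:** recruitment was still under way when the article, with its block size, was written.

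**The concern.** A sealed envelope hides the next card, but it does not hide what the earlier cards imply. In a fixed block of 10 with five places per arm, once five cards of one arm have been opened, every remaining card in that block is known. Here there is one sequence, with no strata or other sites to break it up. The people who recruit open the envelopes, and the block size is in print during recruitment.

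Selection bias is at stake. A researcher who knows or suspects the next arm can, even without intending to, bring an enrolment forward, delay it, or encourage consent more or less warmly. The arms could then differ in severity, motivation or likely engagement before treatment starts. Blind outcome assessment does not protect against this, because the bias enters at enrolment.

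**Working it through.** The article gives no figure for predictability, so there is none to reproduce.

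**Inputs.** Block size 10 (Sequence generation {16a}); 80 patients (Sample size {14}), so 80 / 10 = 8 blocks; two arms (Abstract, Methods). Assumed: 1:1 allocation (five per arm in each block), every block of size 10, and enrolling staff who know the block size and all earlier openings.

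**Allocations known with certainty.** There are C(10,5) = 252 equally likely blocks. The allocation after the first k is forced if one arm has used its five places within those k. This happens in 2 × C(k,5) of the 252 blocks:

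| Place in block | k | Blocks in which it is forced | Share |
|---|---|---|---|
| 6th | 5 | 2 × 1 = 2 | 0.8% |
| 7th | 6 | 2 × 6 = 12 | 4.8% |
| 8th | 7 | 2 × 21 = 42 | 16.7% |
| 9th | 8 | 2 × 56 = 112 | 44.4% |
| 10th | 9 | 2 × 126 = 252 | 100% |

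Sum: 2 + 12 + 42 + 112 + 252 = 420. Expected forced allocations per block: 420 / 252 = 1.667. The closed form for a 1:1 block of size 2m agrees: 2m/(m + 1) = 10/6. As a share this is 1/(m + 1) = 1/6 = 16.7%. Over eight blocks: 8 × 1.667 = 13.3 of 80. The last place is always forced, and at least two places are forced in 44.4% of blocks.

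**Best guess.** Naming the arm with more places left, and tossing a coin when they are equal, gives 6.53 correct of 10 on average over the 252 blocks: 65.3%, against 50% by chance.

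**Sensitivity to the ratio.** At 6:4 per block the forced share is 17.7%, and at 7:3 it is 21.3%. Of these ratios, 1:1 gives the smallest share.

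**Effect of varying the block size.** Sequences of 80 were simulated with each block drawn at random from a set of sizes. The enroller was assumed to know the set and all past allocations, but not the size of the current block.

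| Block sizes | Certain in advance | Best guess correct |
|---|---|---|
| 10 only | 16.7% | 65.3% |
| 6, 8, 10, 12 | 0.9% | 65.3% |

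With 6, 8, 10 and 12, 0.009 × 80 = 0.7 patients would be certain in advance, instead of 13.3. Best-guess accuracy does not move.

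**The case against.** Several points on the other side stand.

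- **The figure is a ceiling.** It needs 1:1 allocation, knowledge of the block size and full tracking. The article states no ratio. It speaks of researchers in the plural and does not say that they share a log. Less sharing would lower the share.
- **Ten is not a small block.** Fixed 1:1 blocks of 4, 6 and 8 would force 33%, 25% and 20%.
- **Safeguards exist.** The envelopes were prepared independently, and outcome assessors and analysts are blind. These protect the next card and the outcome ratings, but not against deduction from past cards.
- **Eligibility leaves little room to turn a patient away.** Eligibility criteria {10} takes all consenting patients, with only three diagnostic exclusions. The timing of enrolment and encouragement to consent remain open to influence.
- **Part of any imbalance is handled.** Statistical methods {20a} defines the outcome as residual gains, which normally adjusts for the baseline score.

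A reader might infer that one allocation in six was in fact known, that the whole site is unblinded, or that any bias would be invisible and beyond repair. The article supports none of these. It shows what could be deduced, not what was. Assessors and analysts are blind. Imbalance in a measured baseline variable can be seen and partly adjusted for. Only selection on unmeasured factors, such as motivation, could not be reliably removed by analysis.

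**Conclusion.** The concern holds as a weakness of the allocation procedure. Assuming 1:1 allocation and enrolling staff who know the block size and follow earlier openings, an average of 1.67 allocations per block (16.7%, about 13 of 80) could be deduced with certainty before enrolment. The setting makes this feasible: one clinic, one unstratified sequence, enrolment and envelope opening in the same hands, and a block size printed during recruitment. It is worth correcting for any envelopes still unopened. It does not show that the allocations already made are biased.

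**What to change.** For the unopened remainder, the trial-independent researcher should generate a new sequence with randomly varying block sizes (for example 6, 8, 10 and 12). The sizes should be withheld from enrolling staff and left unpublished until recruitment closes. State that each envelope is opened only after consent and inclusion are recorded; the present text says only that it happens at inclusion.

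As a check on patients already randomised, compare baseline ZAN-BPD by arm at forced and unforced positions. With about 13 forced positions even in a full trial, this could show only a gross imbalance and would not rule out selection on unmeasured factors.

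The change removes nearly all certain foreknowledge, but it should not be presented as lowering the 65% guessing rate.

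Cost: an amendment approved by the ethics committee (Plans for communicating important protocol amendments {25}), re-issued envelopes, and a possible final imbalance of a few patients. Stopping inside a block of 12 can leave the arms at most 6 apart; switching inside a current block of 10 can add at most 5. Some of this risk exists already: Interim analyses {21b} lets the funding period decide when recruitment ends, so a block of 10 may also be cut short.

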### Concealment mechanism {16b}

The sequence is concealed within sealed envelopes, which were prepared by a trial-independent researcher.

### Implementation {16c}

The allocation sequence is generated by the computer, the concealment by an independent researcher. Then the study researchers enroll the participants and assign participants to interventions, after the opening of the sealed envelope.

## Assignment of interventions: blinding

### Who will be blinded {17a}

The assessors (of outcome and mechanisms) and data analysts will be blind to the experimental condition, but the patients and the therapist will not. In order to control for bias, assessors will be polled at the end of the study with regard to each patient’s condition.

### Procedure for unblinding if needed {17b}

The competent Ethics Committee can request audits at any moment in time and the primary investigator and his team will follow its instructions. Audit may include to disclose, in a restricted fashion and only if deemed necessary, personal data related to participants to the Ethics Committee.

## Data collection and management

### Plans for assessment and collection of outcomes {18a}

All relevant information related to the reliability and validity of the outcome measures are provided under assessments {12}. All interviewers, assessors and raters are extensively trained in the relevant assessment procedures, and reliability is checked continuously. All data are collected in a secure online system, which assures privacy protection and data integrity, as described in the data management plan (see below).

### Plans to promote participant retention and complete follow up {18b}

At follow up, the participants will be contacted by the research team. Importantly, any participant who dropped out of treatment will still be invited for research assessments and follow up.

### Data management {19}

According to the accepted data management plan, data will be entered into RedCap on a secure space on the University server. This program allows full accountability of data management, and standard procedures are in place should problems arise. All details are found in the data management plan, which can be obtained from the primary investigator upon request.

### Confidentiality {27}

Data safety is guaranteed by the system’s security check and no formal data monitoring committee is requested. Participants’ personal information will be stored at a separate, locked, location at the Department of Psychiatry. No personal information will be revealed before, during or after the trial (except in the case of audit by the competent Ethics Committee; plans to give access to the protocol, participant level-data and statistical code are described in the data management plan; see {31c}).

### Plans for collection, laboratory evaluation and storage of biological specimens for genetic or molecular analysis in this trial/future use {33}

This trial does not involve collecting biological specimens for storage.

## Statistical methods

### Statistical methods for primary and secondary outcomes{20a}

For the behavioral assessments and all outcomes, we will conduct intent-to-treat and completer analyses for all variables (hypothesis 1: outcome, defined as residual gains at discharge). We will use multilevel modeling [103] where appropriate, for hypotheses 2 and 3 (global change and treatment response). For hypothesis 4 (mediation), we will conduct a mediation analysis for both potential mechanisms of change [104]. Raw and composite scores for outcome and all mechanisms of change indexes will be used, by controlling for the corresponding fMRI data from the same assessment point. Composite scores for EP involve combining pre-post change in contemptuousness with change in neuronal regions of interest for individualized self-criticism. For SCP, this involves combining pre-post change in CCRT pervasiveness with change in neuronal regions of interest for theory of mind.

We will control for therapist effects in the three-level hierarchical linear modeling (HLM) [105]. All indexes (i.e., behavioral and fMRI) in the patient groups (*N* = 80) at intake will be rigorously compared with the indexes found in the healthy control group (*N* = 20); we expect systematic between-group differences, in the context of a control analysis. Statistical treatment packages HLM7 and SPSS23 will be used for the analyses of the behavioral indexes.

For the fMRI assessments, we will use the methodology of blood-oxygen-level-dependent (BOLD) imaging followed by standard data processing and statistical analysis in the framework of Statistical Parametric Mapping software (SPM12). The fMRI data will be acquired on a Siemens Prisma 3 T (64-channel head coil using a 2D echo planar (EPI) sequence). The acquisition parameters will be as follows: 3 × 3 × 3 mm3: echo time (TE) =30 ms, slice repetition time (TR) = 66 ms, 30 slices, flip angle = 90°. The structural MRI data consist of T1-weighted MPRAGE images (TR = 2000 ms; inversion time (TI) = 920 ms; α = 9°; bandwidth (BW) = 250 Hz/pixel; readout in inferior-superior direction; field of view (FoV) = 256 × 232 mm; 176 slices) at 1 mm resolution. All data pre-processing will be performed using the SPM12 (Wellcome Trust Centre for Neuroimaging, shttp://www.fil.ion.ucl.ac.uk/spm/) running under Matlab 7.13 (The MathWorks, Inc., Natick, MA, USA). EPI images will be realigned to the subject’s average image across trials (corrected for spatial distortions using the SPM fieldmap tools). The parameters of registration to standardized Montreal Neurological Institute (MNI)-defined space will be calculated on the anatomical image and the default settings of the “unified segmentation” framework followed by the diffeomorphic registration algorithm DARTEL [106, 107]. The spatial registration parameters will be applied to the functional time-series co-registered to the corresponding individual’s anatomical scan. Prior to statistical analysis, we will apply spatial smoothing with a Gaussian kernel of 8 mm full-width-at-half-maximum. All statistical analyses will be performed using the default settings in SPM12. The statistical analysis at subject-specific level will be performed using the general linear model (GLM) after convolving the event onsets with a canonical hemodynamic response function [108]. Both time points will be modeled as two separate sessions within the design matrices. For the EP task, at the subject level we will calculate the interaction between words (self-critical versus standard negative words; the non-words and the negative words will be excluded from the analyses, but used as control variables to ensure cognitive appropriateness) and time (time point 1 versus time point 2) using symbols as baseline. For the SCP task, the subject-level differential *t* contrast will test the interaction between ToM, PUN and time point (the control stimuli will be excluded from the data analysis, but will serve as control for cognitive appropriateness). For both tasks, we will use the one-sample *t* test with the outcomes and arousal changes associated with treatment as regressors for the group-level analyses. The differential contrasts at the group level will test for positive and negative correlation between the interaction at the subject-specific level and BOLD signal changes. Where appropriate, we will control for the corresponding behavioral data from the same assessment point.

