### Eligibility criteria {10}

Patients with BPD according to the *Diagnostic and statistical manual of mental disorders, fifth edition* [72] and who have sufficient mastery of French will be included. The rate of comorbidity is expected to be high. All patients who accept participation in the study by giving informed written consent will be included in the outcome and mechanisms parts of the study; a sub-group of patients who fulfil additional inclusion criteria (female, younger than 45 years, right-handed, on stable medication or no medication and absence of formal counter-indication on the security check) will be included in the fMRI part of the study.

Patients with neurocognitive disorder, psychosis and bipolar disorder I will be excluded from the trial. In order to ensure generalizability of the results to a wide variety of clinical settings, no other exclusion criteria will be applied.

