#### Methods in analysis to handle protocol non-adherence and any statistical methods to handle missing data {20c}

Treatments with low adherence scores will still be included in the trial, but the level of adherence on the named scale will be included as a controlled variable on the level of the statistical analyses. For missing values, we will use classical methods of multiple imputations.

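### Section {20a} adjusts outcome and all mechanism scores for same-time fMRI, which only a sub-group has and which is part of the hypothesised mediator; the models and patients it applies to need to be fixed

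*Protocol article*

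**What the plan says.** The first paragraph of {20a} goes through the hypotheses in order. Hypothesis 1 (symptom outcome at discharge) is to be analysed by intent-to-treat and among completers, for all variables. Multilevel models serve hypotheses 2 and 3 where appropriate, and a mediation analysis serves hypothesis 4. The next sentence covers both raw and composite scores and states: "scores for outcome and all mechanisms of change indexes will be used, by controlling for the corresponding fMRI data from the same assessment point". It carries no qualifier. The reverse adjustment at the end of the fMRI paragraph, of imaging results for behavioural data, is made only where appropriate.

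The composites are then defined: "Composite scores for EP involve combining pre-post change in contemptuousness with change in neuronal regions of interest for individualized self-criticism". The socio-cognitive composite is built the same way, from CCRT pervasiveness and theory-of-mind regions.

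Four other places bear on this:

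- Eligibility {10}: every consenting patient enters the outcome and mechanism parts, but the imaging part takes "a sub-group of patients who fulfil additional inclusion criteria (female, younger than 45 years, right-handed, on stable medication or no medication", with a scanner safety check in addition. The abstract also speaks of a sub-sample. Neither gives a number.
- Objectives {7}: change in the mechanisms is defined at both behavioural and neurofunctional level, and hypothesis 4 makes these changes the mediators of symptom decrease.
- {20a}, healthy-control comparison: "All indexes (i.e., behavioral and fMRI) in the patient groups", followed by N = 80, are to be compared with 20 controls.
- {20c}: "For missing values, we will use classical methods of multiple imputations".

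**The concern.** A covariate that exists by design for only part of the sample cannot enter a model meant to include everyone randomised. Unscanned patients either drop out of the model or need an imputed scan. Patients excluded from imaging because of sex, age or handedness have no scanned counterparts with the same characteristic from whom a scan could be imputed.

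The covariate is also measured after randomisation and lies on the causal path that the trial sets out to show. A treatment coefficient for discharge symptoms adjusted for discharge fMRI is the effect that does not pass through the measured neural change. That is a different estimand from the superiority question in hypothesis 1.

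Finally, the composites already contain fMRI change. Controlling them for it undoes the integration of behavioural and neural information that the article gives as its methodological rationale.

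At stake are which patients, and which effect, the main comparison describes.

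**Working it through.** **Inputs from the Sample size section {14}.** "we plan to recruit 80 patients with BPD for this study"; d = "0.60; two-tailed alpha = .05; 30% dropout"; "presumed power 0.819, for two concomitant mechanisms". Equal allocation is assumed (two arms, blocks of 10), so 40 per arm, or 28 per arm after dropout (80 × 0.7 = 56).

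**Reference power.** Two-sample t test, two-sided 0.05, noncentrality d × √(n/2) with n per arm:

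- n = 40: 0.60 × √20 = 2.683, power 0.755.
- n = 28: 0.60 × √14 = 2.245, power 0.597.

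The plan's 0.819 is not reproduced by this comparison. That is a separate matter on which this point does not depend; 0.755 is used here only as the like-for-like reference.

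**1. Restriction to scanned patients.** The scanned share is not given, so the range is assumed. Same formula, complete cases, d = 0.60:

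| Share scanned (assumed) | Scanned of 80 | Noncentrality | Power | Scanned of 56 after dropout | Power |
|---|---|---|---|---|---|
| 30% | 24 | 0.60 × √6 = 1.470 | 0.29 | about 17 | 0.21 |
| 50% | 40 | 0.60 × √10 = 1.897 | 0.46 | 28 | 0.33 |
| 70% | 56 | 0.60 × √14 = 2.245 | 0.60 | about 39 | 0.45 |
| All, no fMRI covariate | 80 | 2.683 | 0.755 | 56 | 0.60 |

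**2. Adjustment for a mediator.** Let a share m of the effect pass through the fMRI measure. The total effect is then 0.60 × (1 − m) direct plus 0.60 × m indirect. A model containing the mediator returns only the direct part:

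- m = 25%: 0.60 × 0.75 = 0.45
- m = 50%: 0.60 × 0.50 = 0.30
- m = 75%: 0.60 × 0.25 = 0.15

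A simulation of 4,000 trials per setting, with every patient scanned, gave mean estimates of 0.46, 0.30 and 0.15. Power for the treatment term was 0.51, 0.31 and 0.16 with 80 patients, and 0.38, 0.23 and 0.12 with 56. The shares m are assumptions. The change of estimand does not depend on how many patients are scanned.

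**3. Composite controlled for its own component.** Write the composite as C = w₁B + w₂F, with B the behavioural change and F the fMRI change. After controlling for F, what remains of C is w₁ × (B net of F); the neural term is gone. If only the fMRI level at one visit is controlled for, the removal is partial.

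**4. Coverage of the imaging indexes.** The abstract and {10} limit fMRI to a sub-group, while the healthy-control sentence in {20a} attaches N = 80 to behavioural and fMRI indexes together.

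**The case against.** The strongest reply is that the sentence belongs to hypothesis 4. It follows the mediation sentence directly and leads into the composite definitions, whereas hypothesis 1 was dealt with earlier in the paragraph with no fMRI covariate. A mediation analysis puts the mediator into the outcome model on purpose, so under this reading that adjustment is not a fault. This reading also fits the intent-to-treat promise better, and it stands as a possibility. Against it, the sentence names *outcome* and all mechanism indexes without restriction. Nor does it rescue the rest: the mediation models would still rest on scanned patients only, and a composite controlled for fMRI would still lose its neural part.

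A second reply is that controlling is used loosely and the composite may itself be the way fMRI is taken into account. That is possible, but the sentence applies the control to composite scores as well as raw ones, so the text should say so.

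Some stronger inferences are not supported:

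- A reader might conclude that the main comparisons lose most of their patients. That needs fewer than 40 of 80 scanned, and no sub-sample size is given.
- A reader might conclude that scans will be imputed for ineligible patients. Section {20c} is one general sentence and does not say that scans never planned count as missing.
- A reader might conclude that a null result would be an artefact of the model. It could equally be true, or reflect limited power in the full sample.
- The N = 80 label can be read as describing the cohort. It is a minor inconsistency in an intake control analysis.

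**Conclusion.** The point holds as a fault in a stated rule. Followed literally, the adjustment in {20a} conflicts with the intent-to-treat statement, conditions discharge outcome on a post-randomisation variable that the trial hypothesises to be a mediator, and takes from the composites one of their own components. Whether hypothesis 1 is affected depends on how the sentence is read, and a wording that allows two estimands for the main comparison needs correcting. The sub-sample and composite problems hold under either reading.

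The sizes are conditional. The adjusted effect is 0.45, 0.30 or 0.15 in place of 0.60 if 25%, 50% or 75% is mediated. Complete-case power is about 0.29 to 0.60 in place of 0.755 if 30% to 70% are scanned, before dropout. The documents fix neither share, so the actual loss cannot be computed.

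**What to change.** In {20a}, state that hypotheses 1 to 3 on symptom and behavioural scores, and the behavioural mediation, are estimated in all randomised patients without post-randomisation fMRI covariates. Confine fMRI and composite models to a separately labelled analysis of the scanned sub-sample, give its size, and do not adjust a composite for the fMRI change it contains. In {20c}, state that patients unscanned by design are excluded from imputation of fMRI values. In the healthy-control comparison, replace or qualify N = 80 for the fMRI indexes so that it agrees with the abstract and {10}.

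This changes wording only and needs no new data; section {25} requires ethics committee approval of amendments. The cost is that the combined behavioural-neural analysis becomes a sub-sample result, smaller and limited to patients who meet the imaging criteria.

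### The emotion-processing and socio-cognitive composites are built from unadjusted pre-post change while the symptom outcome is adjusted for intake, which costs precision and can distort the mediation path in either direction

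*Protocol article*

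**What the plan says.** All of this is in the protocol article, Statistical methods for primary and secondary outcomes {20a}, unless another section is named.

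- **Symptom outcome:** "hypothesis 1: outcome, defined as residual gains at discharge". A residual gain is the discharge score with the part predicted by intake removed.
- **Emotion-processing (EP) composite:** "Composite scores for EP involve combining pre-post change in contemptuousness with change in neuronal regions of interest for individualized self-criticism".
- **Socio-cognitive (SCP) composite:** "For SCP, this involves combining pre-post change in CCRT pervasiveness with change in neuronal regions of interest for theory of mind".
- **Use of the scores:** "Raw and composite scores for outcome and all mechanisms of change indexes will be used, by controlling for the corresponding fMRI data from the same" visit. The covariate named here is concurrent imaging data, not the intake value of the mechanism.
- **Models:** "We will use multilevel modeling [103] where appropriate, for hypotheses 2 and 3 (global change and treatment response"), and "For hypothesis 4 (mediation), we will conduct a mediation analysis for both potential mechanisms of change [104"]. No covariate list is given for either.
- **Imaging:** "Both time points will be modeled as two separate sessions within the design matrices". The subject-level contrast is then a difference between time points.
- **Sample size {14}:** "presumed power 0.819, for two concomitant mechanisms", with d = 0.60, two-tailed alpha .05, 30% dropout and 80 patients.
- **Eligibility criteria {10}:** only a sub-group enters the imaging part, and its size is not stated.

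**The concern.** One paragraph treats the intake value in two ways: it is removed from the outcome and left in the composite mechanism scores. Contemptuousness, CCRT pervasiveness and the imaging responses are all measured at intake, so the adjustment is available.

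A raw change score carries the intake value with a negative sign. Patients who start high tend to show the larger fall, whatever their treatment. Two things are at stake. The arm contrast on the composites is noisier than it need be. And in the mediation analysis (hypothesis 4), a mediator that is partly intake level is related to an outcome from which only the symptom intake score has been removed. Any link between intake mechanism level and later symptoms then leaks into the path that is meant to show how treatment works.

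**Working it through.** **Inputs.** d = 0.60, two-sided alpha .05, 80 patients and 30% dropout (Sample size {14}). Equal allocation is assumed because the ratio is not stated: 40 per arm, or 40 × 0.70 = 28 after dropout. ρ, the intake-to-discharge correlation of the mechanism score, is not in the article and is varied from 0.3 to 0.8. The variance σ² is assumed equal at both times.

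**The plan's own figure.** A two-sample t-test with these inputs has power 0.755 at 40 per arm and 0.597 at 28 per arm. The stated 0.819 is not reproduced. That is a separate matter; nothing below uses 0.819.

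**Step 1: precision of the arm contrast.** Var(change) = 2σ²(1 − ρ). Variance of the discharge score given intake = σ²(1 − ρ²). The ratio is (1 + ρ)/2, so adjustment saves (1 − ρ)/2. The correlation of change with intake is −√((1 − ρ)/2).

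| ρ | Variance saved | Correlation of change with intake |
|---|---|---|
| 0.3 | 35% | −0.59 |
| 0.5 | 25% | −0.50 |
| 0.7 | 15% | −0.39 |
| 0.8 | 10% | −0.32 |

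**Step 2: what that means for power (illustration only).** The composites exist only for scanned patients, whose number is not given, so 28 or 40 per arm is not their sample. The article also does not say which SD d refers to.

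| Scale of d | n per arm | ρ = 0.3 | ρ = 0.5 | ρ = 0.7 |
|---|---|---|---|---|
| SD of change | 28 | 0.60 → 0.78 | 0.60 → 0.72 | 0.60 → 0.67 |
| SD of change | 40 | 0.755 → 0.91 | 0.755 → 0.86 | 0.755 → 0.82 |
| SD of discharge score | 28 | 0.46 → 0.64 | 0.60 → 0.72 | 0.81 → 0.87 |

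Each cell shows change score → intake-adjusted. In the first two rows the adjusted effect is 0.60 × √(2/(1 + ρ)). At ρ = 0.8, on the discharge-score scale with 28 per arm, the gain is only 0.94 → 0.96.

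**Step 3: bias of the arm contrast.** In simulation (28 per arm, true arm effect 0.60 in the direction of a fall), both analyses return about −0.60. Randomisation makes regression to the mean equal in expectation across arms.

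**Step 4: the mediator-to-outcome path.** Let the residual outcome be Y = bΔ + sM₀ + e within arm, where Δ is mechanism change and M₀ the intake level. Regressing Y on arm and Δ alone gives

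b + s × Cov(M₀, Δ)/Var(Δ) = b + s × (ρ − 1)σ²/[2(1 − ρ)σ²] = b − s/2.

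For s = 0.2 and 0.3 the bias is −0.10 and −0.15. Simulation with b = 0 gives the same values.

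False-positive rate at ρ = 0.5, 28 per arm and unit error variance: the correlation of Δ with Y is −(s/2)/√(1 + s²), which is −0.098 and −0.144. Multiplying by √53 = 7.28 gives expected t of about −0.71 and −1.05. The two-sided rejection rates are then about 0.11 and 0.18. Simulation gave 0.11 and 0.18 to 0.20. With intake in the model the rate is about 0.05. With s = 0 it is about 0.05 either way.

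**Step 5: direction.** Falling contemptuousness or pervasiveness should go with lower residual symptoms, so hypothesised mediation needs b > 0. If higher intake levels predict worse residual symptoms (s > 0), the bias is negative and hides mediation. If s < 0, it imitates mediation.

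**The case against.** The strongest reply is that the text commits to change scores only in part. Plain change is written down for the two composites and the imaging contrasts. Raw mechanism indexes are used as well, and hypotheses 2 and 3 go to multilevel models. A reader might infer that every mechanism analysis is a change-score analysis; the article does not say so. Nor can the multilevel models be dismissed as the same thing. That equivalence needs two time points and freely estimated intake means, whereas the article lists four assessments and does not give the parameterisation.

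A reader might also infer that intake is left out of the mediation model. The covariates are simply not listed, and a condensed article may leave them to a fuller document. What remains is the stated construction of the composites.

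Two further inferences fail. Regression to the mean does not bias the randomised comparison (step 3), and chance intake imbalance is the same precision loss counted once, not a second harm. The intake artefact cannot be described only as false mediation, because with s > 0 it hides mediation.

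Finally, hypotheses 2 and 3 in Objectives {7} are worded as change, and responders are not a randomised group. For that comparison, change and intake-adjusted analyses answer different questions, and adjustment is not automatically better. This stands, and the fix leaves that comparison alone.

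**Conclusion.** The point holds for the EP and SCP composites. The article adjusts the outcome for intake and, in the same paragraph, specifies composites that are not adjusted.

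For the arm contrast the cost is precision only: 10% to 35% of the variance over ρ from 0.8 to 0.3, assuming equal variances. The loss in power cannot be fixed because neither ρ nor the size of the imaging sub-sample is given.

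For mediation with the composite as mediator and intake not otherwise in the model, the bias is about −s/2. At ρ = 0.5 and 28 per arm this raises the false-positive rate of the path from 0.05 to roughly 0.1 to 0.2 for s of 0.2 to 0.3 in either direction. The bias depends on s, about which the article says nothing, and vanishes at s = 0. The change is worth making because it is cheap and mediation is a central aim, but the point does not invalidate the mechanism analyses as a whole.

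**What to change.** In section {20a}:

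1. Form the EP and SCP composites from intake-adjusted (residualised) mechanism scores, as for the symptom outcome, using region-of-interest values extracted separately for each scanning session.
2. In the mediation analysis, include the intake mechanism value and intake ZAN-BPD in both the mediator and the outcome equations.
3. Where raw behavioural indexes are compared between arms, adjust for the intake value or constrain intake means to be equal across arms.
4. Keep raw pre-post change as a descriptive summary. Leave the SPM subject-level contrasts and the descriptive responder comparison (hypothesis 3) as they are.

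The cost is one or two degrees of freedom per model, the per-session extraction of region values and a little extra analysis work. No additional data collection is needed.
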